#### Patient and public involvement

This trial was designed by investigators in accordance with previous clinical experience and pertinent literature. No patients were involved in the design of this study. All participants will be guided to learn Baduanjin exercise through 8 educational courses. We will also give general information about IR-PCOS in these courses and encourage the participants to ask questions and give us feedback to ensure the smooth progress of this trial. The cost of drug interventions and laboratory tests, and the registration fees during follow-up will be covered by study fundings so it will not be a significant burden and will be in line with participants preferences. We will also send out a summary of their own clinical data and the study results to all participants at the completion of the trial.

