### Interventions

After baseline measurements, participants satisfying the inclusion criteria will be randomly divided into one of the following 5 clinical groups:
Group A: metformin at a dose of 500 mg per meal, 3 times per day, orally for 2 courses.Group B: BSHTD at a total dose of 400 ml per day, divided into 2 oral, doses for a total of 2 courses.Group C: Baduanjin exercise for 30 min per day, for a total of 2 courses.Group D: BSHTD combined with metformin, orally for 2 courses.Group E: BSHTD combined with Baduanjin exercise, for a total of 2 courses.

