#### Group C: Baduanjin exercise

The Baduanjin exercise newly promulgated by the Ministry of Sport of China in 2003 will be adopted in this trial. We will guide the patients to learn Baduanjin exercise through 8 courses and ensure that all participants can master standard movements. After that, the patients will consciously perform these exercises at home once a day, for 30 min each session, and will stop during menstruation. One course of treatment is three months long, and patients will be given a total of two courses. We will provide free training videos and daily training registration cards to urge and monitor practice attendance.

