#### Group E: Bushen Huatan decoction combined with Baduanjin exercise

The daily oral solution of Bushen Huatan Decoction is similar to that of group B; in addition, the participants in this group are required to practice Baduanjin exercise during the stage of the trial (the specific exercise program is similar to that of group C). All interventions will be stopped during menstruation. One course of treatment is three months long, and patients will be given a total of two courses.

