## Discussion

As far as we are aware, no previous investigation has discussed whether Baduanjin exercise has therapeutic potential in IR-PCOS. Our research is the first randomized controlled trial to compare the efficiency of a combination of TCM and behavioural therapy in the treatment of IR-PCOS. Each aspect of this trial was fully discussed by the research group, and this protocol was unanimously approved by the group. The assumptions of this trial are as follows: Bushen Huatan Decoction shows equivalent clinical effects as the single-use of metformin; the efficiency of Bushen Huatan Decoction combined with metformin is superior to that of a single-use of metformin; the efficiency of Bushen Huatan Decoction combined with Baduanjin exercise is superior to that of Bushen Huatan Decoction and Baduanjin exercise; and the efficiency of Bushen Huatan Decoction combined with Baduanjin is equal to that of Bushen Huatan Decoction combined with metformin.

From the perspective of TCM syndrome differentiation and treatment, kidney deficiency and phlegm dampness are mainly responsible for the pathogenesis of IR-PCOS, so the central focus of treatment should be on tonifying the kidney, invigorating the spleen and reducing phlegm, while paying attention to lifestyle modification in the course of treatment. It is worth noting that patients with IR-PCOS appear to have a higher risk of irregular diet and lifestyle. However, taking weight-loss drugs for a long time is not a sustainable solution for overweight patients; from this, we developed a comprehensive intervention program that combines TCM with Chinese fitness Qigong Baduanjin for the treatment of patients with IR-PCOS. On the one hand, a lifestyle-based intervention program can provide considerable benefits, such as body weight loss and improvements in physical signs of hyperandrogenism. On the other hand, the program can improve the psychosocial status of patients and provide a better quality of life. Additionally, a social network platform will be established to motivate and encourage the patients throughout the intervention and follow-up phases.

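### The article says all participants are taught Baduanjin, but the interventions section gives it to groups C and E only; on either reading, E versus B does not cleanly isolate Baduanjin.

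*Protocol article*

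**What the plan says.** The Interventions section lists Baduanjin for group C ("Group C: Baduanjin exercise for 30 min per day, for a total of 2 courses") and, combined with BSHTD, for group E. Groups A and B have no exercise component, and neither has group D ("Group D: BSHTD combined with metformin, orally for 2 courses").

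The teaching is described under the group C heading: "We will guide the patients to learn Baduanjin exercise through 8 courses and ensure that all participants can master standard movements". Daily home practice follows, with materials and attendance records: "We will provide free training videos and daily training registration cards to urge and monitor practice attendance". For group E, "the participants in this group are required to practice Baduanjin exercise during the stage of the trial", on a programme like that of group C.

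Patient and public involvement, which has no group heading, says "All participants will be guided to learn Baduanjin exercise through 8 educational courses" and adds "We will also give general information about IR-PCOS in these courses".

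The Discussion hypothesises that E is superior to B and to C, and that E is equal to D.

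**The concern.** The five arms contain one clean test of adding Baduanjin: E (BSHTD plus Baduanjin) against B (BSHTD). If B attends the same eight courses, the comparator receives the instruction part of the tested intervention. The exercise is done at home and self-directed, so someone who has learned it can do it unprompted.

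Nothing in the article asks A, B or D not to practise. Nothing records whether they do: registration cards appear only in the Baduanjin programme, and the visits are said to capture clinical progress, adverse events and additional medication. Under the intention-to-treat analysis that is planned, any such practice would be built into the estimate and could not be examined afterwards.

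**Working it through.** **1. Which pairs isolate what.**

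| Pair | Differs by |
|---|---|
| E − B | Baduanjin |
| E − C | BSHTD |
| D − A | BSHTD |
| D − B | metformin |
| E − D | Baduanjin in place of metformin, on BSHTD |
| C − A | Baduanjin in place of metformin |

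Only E − B gives the added effect of Baduanjin.

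**2. The two readings of the sentence.**

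- *Whole trial.* A, B and D are taught the exercise, which contradicts the Interventions section and the group C and E descriptions.
- *C and E only.* The contradiction goes. But the IR-PCOS information is given in these courses, so the article describes it only for C and E. E − B is then Baduanjin plus education.

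**3. Direction of any contamination.** Let b be the Baduanjin effect, taken as beneficial, and c the share of a comparator arm that practises with full effect.

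- E − B becomes b(1 − c), which is always nearer zero.
- E − D becomes Δ − cb, where Δ is the true difference. The shift is against E. It moves toward equality only if E is truly better than D. If Δ = 0, it moves away from equality.
- C − A shifts against C in the same way.
- E − C does not change, because both arms are assigned Baduanjin.

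**4. The plan's own figures.** From Sample size calculation: changes of 0.40 ± 0.24 (metformin) and 0.57 ± 0.27 (BSHTD plus metformin), two-sided 5%, 30 evaluable per group, 20% attrition.

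- Pooled SD = √[(0.24² + 0.27²)/2] = 0.255.
- Attrition: 30/(1 − 0.20) = 37.5, so 38 per group and 190 in total. This reproduces.
- Five-group ANOVA power: the article does not give the five means. With 0.40 for A, B and C and 0.57 for D and E, which is an assumed pattern that fits the Discussion's hypotheses, power is about 90%. This matches the stated figure.

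**5. Illustration of dilution in E − B.** Assumptions: b = 0.57 − 0.40 = 0.17, borrowed from BSHTD added to metformin because no Baduanjin effect is given; SD 0.255; n = 30 per arm; unadjusted two-sided t test at 5% (58 degrees of freedom). The uptake rates are also assumed.

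Standard error = 0.2554 × √(2/30) = 0.0660. Noncentrality = 0.17(1 − c)/0.0660.

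| Uptake c in B | E − B | Noncentrality | Power |
|---|---|---|---|
| 0 | 0.170 | 2.58 | 72% |
| 20% | 0.136 | 2.06 | 53% |
| 30% | 0.119 | 1.80 | 43% |
| 50% | 0.085 | 1.29 | 25% |

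A normal approximation gives 73% at c = 0, 49% at 25% and 25% at 50%, which agrees. The sample size needed rises by 1/(1 − c)²: 1.56 times at 20% and 4 times at 50%. That multiplier does not depend on the assumed effect or SD.

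The 72% with no uptake reflects a single pairwise test at 30 per arm and is a separate matter. Only the fall from it concerns contamination.

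**The case against.** The strongest reply is loose wording. Under the group C heading, almost the same sentence, about the same eight courses, also speaks of all participants, and there it can only mean those assigned Baduanjin. The involvement section assigns no treatment, and the text that does assign it is consistent. This reading is plausible but not settled. The involvement section has no group heading, and its last sentence uses the same phrase for everyone in the trial. The narrower reading also leaves the education difference in E versus B.

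Three further points stand as limits:

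- **Teaching is not practice.** Daily practice is required only in C and E, so even the literal reading does not show that anyone in A, B or D will exercise.
- **The power figures are hypothetical.** Neither the 0.17 as a Baduanjin effect nor the uptake rates have a source in the article.
- **Two stronger inferences fail.** A reader might infer that contamination pushes E and D toward a false finding of equality. The documents do not support this: it requires E to be truly better than D, whereas the Discussion hypothesises that they are equal, and then the shift is away from equality. A reader might also take the Discussion's statement that "a social network platform will be established to motivate and encourage the patients throughout the intervention and follow-up phases" as a second route of contamination. It does not say that the platform is shared across arms or that it carries Baduanjin material, and it closes a paragraph about the combined programme.

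**Conclusion.** The concern holds in limited form. The article contradicts itself on who is taught Baduanjin, and neither reading leaves E versus B, a stated superiority hypothesis, as a clean test of the exercise. On the literal reading the comparator is taught the tested component, and any beneficial practice in B pulls the estimate toward zero. On the narrow reading the estimate also contains disease education.

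E versus D and C versus A could shift against the Baduanjin arm, but whether toward or away from equality depends on true effects that nobody knows. E versus C is unaffected.

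The size cannot be established from the article. The fall from about 72% to 53% or 25% rests on the borrowed effect, the pooled pilot SD, 30 evaluable per arm and full-effect uptake of 20% or 50% in B. It shows sensitivity and is not a forecast. The inconsistency deserves correction because contamination that has not been recorded cannot be repaired in the analysis.

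**What to change.** Reconcile Patient and public involvement with the Interventions section and the group C and E descriptions:

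1. State that Baduanjin teaching and training videos go to groups C and E only.
2. Give the same general IR-PCOS information, with the same chance to ask questions, to all five groups; in A, B and D without exercise teaching.
3. Ask A, B and D about Baduanjin practice at existing visits and record the answer, so that any crossover can be described.

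The cost is a change of wording, separate session lists for information and for exercise teaching, and one extra question at visits already planned. Separate information sessions need some added organisation. Sample size and analysis method need not change for this point.

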### Study-specific visits and procedures

All participants will receive 2 courses of treatment lasting for 6 months and will be followed up for 6 months. All participants will attend a total of 6 visits: screening visit, baseline visit, first course visit, end-of-treatment visit, and two follow-up visits. Simultaneously, close monitoring of possible adverse events during the trial process will be performed. A flowchart of this trial is depicted in Fig. 1. The schedule of trial enrolment, intervention and assessment is expounded in Table 1.

**Fig. 1 Fig1:**
[figure not shown]
Flow chart of the trial

**Table 1 Tab1:**
[figure not shown]
Schedule of enrolment, intervention and assessment

### Outcome measurements

#### Primary outcomes

The primary outcomes are changes in HOMA-IR (calculated according to the fasting plasma glucose and serum insulin) and improvements in the oral glucose tolerance test (OGTT) and insulin-releasing test (INS).

#### Secondary outcomes

The secondary outcomes will include the levels of basic serum sex hormones [including luteinizing hormone (LH), follicle-stimulating hormone (FSH), oestradiol (E_2_), testosterone (T), progesterone (P), prolactin (PRL), dehydroepiandrosterone (DHEAS), and sex hormone binding globulin (SHBG)], the ovulation rate in each menstrual cycle, the clinical pregnancy rate, BMI, FAI, Ferriman-Gallwey scores, TCM syndrome scores and security index tests (including routine blood examination, routine urine and stool tests, hepatic and renal function, and ECG examination).

All the participants will be instructed to return to visit the doctor every week. They will be contacted by phone if they miss a scheduled appointment. All clinical progress, adverse events and additional medication use will be recorded at every visit.

### Sample size calculation

The sample size calculated by Power Analysis & Sample Size (NCSS-PASS 11.0) was assessed based on HOMA-IR, which is the most significant outcome in this trial. In our pilot study (according to the research results of [name] doctoral thesis) evaluating the effect of metformin and BSHTD on HOMA-IR in patients with IR-PCOS, the results showed that HOMA-IR decreased from 2.11±0.30 to 1.71±0.26 in the metformin treatment group and the difference before and after treatment was 0.40±0.24, while HOMA-IR of Bushen Huatan Decoction combined with metformin treatment group decreased from 2.09±0.30 to 1.52±0.26 and the difference before and after treatment was 0.57±0.27. Therefore, we used the minimum sample size required to evaluate effectiveness [18]. We anticipate that after two courses of treatment, HOMA-IR of Bushen Huatan Decoction combined with metformin group will decrease by 30%, and HOMA-IR of single-use of metformin group will decrease by 20%. Therefore, the difference is 10%,with two-sided α assigned to be 5% and *β* 20% at the upper limit, respectively, at which the power is 90% and the rate of attrition estimated to be 20%. In a one-way ANOVA study, sample sizes of 30, 30, 30, 30, and 30 were obtained for the 5 groups whose means are to be compared. A total sample size of 150 subjects achieves 90% power to detect differences among the means versus the alternative of equal means using an F test with a 5% significance level. By enrolling 38 participants in each group, we allow the rate of attrition to be estimated to be 20%.

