#### Inclusion criteria

Chinese women aged from 18 to 35 years old.BMI [13] over 25.0 kg/m^2^.Confirmed diagnosis of PCOS according to the 2003 Rotterdam criteria [14]: (a) irregular menstruation cycles (a periodic interval > 35 days or < 8 cycles in a year) or amenorrhoea (a periodic interval > 90 days) or abnormal uterine bleeding; (b) clinical manifestations of hyperandrogenism (hirsutism in mainland China is taken as Ferriman-Gallwey score ≥5 [15]) and/or hyperandrogenemia [free androgen index (FAI)=total testosterone (nmol/L)/SHBG (nmol/L)×100 > 4.5 [16]]; and (c) transvaginal ultrasonography showing PCOM: the number of follicles with a diameter of 2–9 mm in one or both ovaries ≥12, and/or ovarian volume ≥10 ml [ovarian volume calculation: 0.5 × long diameter (cm) × diameter (cm) × anteroposterior diameter (cm)]. Among all the above, (a) is a necessary condition, and matching one of (b) or (c) represents suspected PCOS, which then requires ruling out other factors and diseases that may cause hyperandrogenism and ovulation dysfunction.In line with the diagnosis criteria of TCM syndrome differentiation: kidney deficiency and phlegm dampness.Confirming the diagnosis of insulin resistance: the criteria of IR are defined according to the homeostatic model assessment of insulin resistance (HOMA-IR) [fasting plasma glucose (mmol/l) × fasting serum insulin (uIU/ml)/22.5]. A value ≥2.29 [17] is considered to be indicative of IR.No history of using hormone drugs or drugs that affect glucose metabolism within the 3 months prior to treatment.Volunteer to participate in this trial and give informed consent.

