### Statistical analysis

Clinical data of all participants will be disposed in the final statistical analysis based on the intent-to-treat principle to determine the robustness of the evidence. The data processors will be unaware of the specific allocation situation. Basic indicators will be analysed to test the balance of each group at baseline. Comparisons will be processed based on changes from baseline to the end of the intervention and follow-up. The one-sample Kolmogorov-Smirnov test and graphical methods will be applied to test the normal distribution of continuous variables (such as the levels of basic serum sex hormones, HOMA-IR, ovulation rate, clinical pregnancy rate, BMI, FAI, Ferriman-Gallwey scores and TCM syndrome scores), which will be presented as the mean ± standard deviation if normally distributed and as the median with an interquartile range if not normally distributed. A paired *T* test or the Wilcoxon rank test will be used to compare variables within a group from baseline to the end of the intervention. Analysis of variance (ANOVA) with Bonferroni correction will be carried out to compare differences among groups of continuous variables consistent with a normal distribution. Continuous variables that do not meet the normal distribution will be processed by using the Kruskal-Wallis test followed by the Mann-Whitney *U* test. Categorical variables will be analysed by chi-square statistics when appropriate, and Fisher’s exact test will be used to compare discrete variables with fewer than 5 observations. All data analyses will be processed by the Statistical Package for Social Sciences (SPSS) version 25.0. A *P* value < 0.05 with a two-tailed test and mean difference with 95% confidence intervals will be considered statistically significant.

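### The HOMA-IR target is a percentage fall, its SDs are for raw change, and the analysis compares an unadjusted change on no stated scale

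*Protocol article*

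**What the plan says.** All references are to the protocol article.

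- **Sample size calculation, pilot.** Results are raw subtractions. For metformin, "HOMA-IR decreased from 2.11±0.30 to 1.71±0.26 in the metformin treatment group and the difference before and after treatment was 0.40±0.24". For the combination, HOMA-IR "decreased from 2.09±0.30 to 1.52±0.26 and the difference before and after treatment was 0.57±0.27".
- **Sample size calculation, target.** The text then moves to percentages: 30% in the combination group, and "HOMA-IR of single-use of metformin group will decrease by 20%. Therefore, the difference is 10" per cent. No SD of percentage change is given. The size is justified by a five-group one-way ANOVA: "A total sample size of 150 subjects achieves 90% power to detect differences among the means", "using an F test with a 5% significance level".
- **Primary outcomes.** "The primary outcomes are changes in HOMA-IR (calculated according to the fasting plasma glucose and serum insulin"). Raw, percentage or log is not specified.
- **Statistical analysis.** "Comparisons will be processed based on changes from baseline to the end of the intervention and follow-up". Groups are compared by ANOVA with Bonferroni correction, or by rank tests if normality fails, with a mean difference and 95% confidence interval. No relative or log scale and no baseline covariate is named.
- **Inclusion criteria.** For HOMA-IR, "A value ≥2.29 [17] is considered to be indicative of IR". No upper limit is set.

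**The concern.** A percentage fall and a raw fall are interchangeable only when all women start at nearly the same HOMA-IR. The pilot came close to that (SD 0.30 on a mean of about 2.10). The trial may not, because it recruits from 2.29 upwards with no ceiling.

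If treatment acts proportionally, women with high baselines have larger raw changes. That spread enters the error term of an unadjusted comparison, and the result in HOMA-IR units cannot be read directly against a 10-point target.

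Even on the pilot's figures, leaving baseline out of the model gives away precision that costs nothing to keep.

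**Working it through.** **1. The plan's own figure.** The five group means and the common SD behind 30 per group are not given, so the figure cannot be rebuilt from stated inputs alone.

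- Pooled raw SD = √[(0.24² + 0.27²)/2] = 0.255.
- F-test noncentrality λ = nΣ(μᵢ − μ̄)²/σ², with n = 30 and σ² = 0.0653.
- Pilot raw difference 0.57 − 0.40 = 0.17, with A = B = C and D = E: Σ = 3(0.068²) + 2(0.102²) = 0.0347, λ ≈ 15.9, power 90.1%.
- Ten per cent of 2.10 = 0.21, with one group different: Σ = 4(0.042²) + 0.168² = 0.0353, λ ≈ 16.2, power 90.6%.

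Both patterns are assumptions. Others tried at the same SD need 20 to 71 per group. Attrition does reproduce: 30/0.8 = 37.5, so 38, and 5 × 38 = 190.

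**2. The two statements of effect differ.** The pilot falls are 0.40/2.11 = 19.0% and 0.57/2.09 = 27.3%, a raw difference of 0.17. The stated 10 points on 2.10 is 0.21. For D against A at 90% power, n = 2(1.960 + 1.282)²σ²/δ² gives 48 per group for 0.17 and 32 for 0.21.

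**3. Power on the pilot's own figures.** Setting: D against A, 30 per arm, two-sided 5%, falls of 20% and 30% from 2.10 (difference 0.21).

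- Implied baseline-to-end correlation r = (0.30² + 0.26² − SD²)/(2 × 0.30 × 0.26). Metformin: (0.1576 − 0.0576)/0.156 = 0.64. Combination: (0.1576 − 0.0729)/0.156 = 0.54.
- Raw change, unadjusted: 0.21/(0.255 × √(2/30)) = 3.19, power about 88% by t test.
- Raw scale with baseline covariate: residual SDs 0.26√(1 − r²) = 0.200 and 0.218, pooled 0.209; 0.21/(0.209 × 0.258) = 3.89, power about 96-97%.
- Simulation of bivariate normal data with these values gives about 88% for raw change, 94-95% for percentage change or log ratio, and 96-97% with baseline as covariate on either scale.

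**4. Baseline spread in the trial.** The pilot CV is 0.30/2.10 = 0.143. If pilot baselines were roughly normal (an assumption), the share at or above 2.29 is P(Z > 0.19/0.30) ≈ 26%. The pilot therefore does not describe the trial population.

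**5. Sensitivity to that spread if the effect is proportional (assumption).** Raw change = baseline × fractional fall p, so Var = μ²[s²(1 + CV²) + p²CV²]. Solving at the pilot SD and CV with p = 0.25 gives s ≈ 0.115. For power, p² is averaged over the arms: (0.04 + 0.09)/2 = 0.065.

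| Baseline CV | Raw change | Percentage change |
|---|---|---|
| 0.143 (pilot) | 89% | 92% |
| 0.3 (assumed) | 78% | 92% |
| 0.4 (assumed) | 68% | 92% |
| 0.5 (assumed) | 57% | 92% |

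Example at CV 0.5: 0.0132 × 1.25 + 0.065 × 0.25 = 0.0328, SD 0.181; 0.10/(0.181 × 0.258) = 2.14, power 57%. Simulation with baselines cut off at 2.29 agrees: 77% at CV 0.31 and 57% at CV 0.52. If the pilot distribution is simply cut off at 2.29, the CV is 0.06 and both scales have about 90%.

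**6. If the effect is additive (assumption).** The order reverses. At CV 0.5, raw change keeps 88% and percentage change drops to 55%; the unadjusted log ratio is similarly weak (about 55% against 87% for raw change at CV 0.54).

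**7. Baseline adjustment.** Under the proportional model at CV 0.5, raw change with a baseline covariate recovers to 84%, from 57% unadjusted. Log HOMA-IR with log baseline holds about 87-88% under the proportional model and roughly 80-88% under the additive one.

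**The case against.** The strongest reply is that the protocol never says raw, so the mismatch is partly read in. The final scale could be settled in an analysis plan that is not shown. The percentages may merely round the pilot's 19% and 27%, and 30 per group can be matched with raw SDs, so sizing and analysis may share a raw scale. At the only documented baseline spread, raw change sits within about two points of the stated 90%.

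Much of this stands. Raw change is the plain reading, because the sample size section itself reports change by subtraction and the analysis section reports a mean difference, but it remains a reading. The match to 30 per group needs patterns of means that the protocol does not state. What does not fall away is that the article itself writes the target on one scale and gives SDs on another, and then describes an unadjusted comparison on no named scale.

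A reader might infer that the trial is seriously underpowered, with power near 60%, or that it does not test the effect it planned. The documents do not support either. The low figures need baseline CVs that the protocol does not give and a constant proportional effect for each woman; the protocol states expected falls only at group level. A reader might also conclude that moving to an unadjusted percentage or log ratio is enough. It is not: that choice is the weaker one if the effect is additive.

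**Conclusion.** The point holds as an inconsistency of scale together with an avoidable loss of precision. On the pilot's own SDs and correlations, the unadjusted raw comparison of D with A has about 88% power, against 94-95% on a relative scale and 96-97% with baseline adjustment. Larger losses, to between 78% and 57%, are conditional on a proportional effect and assumed baseline CVs of 0.3 to 0.5; under an additive effect there is no loss.

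The power figures in steps 3 and 5 to 7 are for one two-arm comparison at 5% with 30 completers per arm. They are not the power of the five-group F test or of the Bonferroni comparisons. They show the relative merit of the analyses, not the trial's overall power. The change is worth making because it is nearly free and protects against a baseline spread that nobody yet knows.

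**What to change.** Use one scale in the primary outcome, sample size and statistical analysis sections.

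- **Outcome and analysis.** Analyse log HOMA-IR at the end of the second course, with treatment group as factor and log baseline HOMA-IR as covariate. Report ratios of geometric means with 95% confidence intervals.
- **Sample size.** State the planned D to A ratio, 0.70/0.80 = 0.875. Give the SD on the log scale, computed from the pilot data, and a baseline distribution compatible with entry at 2.29 or above. State the group means assumed for the F test.
- **Description.** Keep mean raw changes as descriptive results.

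The cost is a wording change and a recalculation from data already held, with no new measurements. The downside is that results are read as ratios rather than HOMA-IR units. Some power is also lost relative to baseline-adjusted raw change if the effect is truly additive.

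### The quoted 90% power is for a five-group F test; the pairwise claims the trial will make have less, markedly so once the plan's Bonferroni correction is applied

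*Protocol article*

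**What the plan says.** All planning figures are in the protocol article under Sample size calculation. The pilot data cover two arms only. HOMA-IR "decreased from 2.11±0.30 to 1.71±0.26 in the metformin treatment group", and for that arm "the difference before and after treatment was 0.40±0.24". For BSHTD plus metformin, "the difference before and after treatment was 0.57±0.27". From these the authors anticipate falls of 30% (D) and 20% (A), a difference of 10%. The error rates are given as "two-sided α assigned to be 5"% and a β of "20% at the upper limit, respectively, at which the power is 90"%.

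The calculation itself is a one-way ANOVA: "sample sizes of 30, 30, 30, 30, and 30 were obtained for the 5 groups", and "150 subjects achieves 90% power to detect differences among the means versus the alternative of equal means using an F test". Allowing for 20% attrition gives 38 per group and 190 in total. No means are given for groups B, C or E, and no SD is named for the F test.

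The Discussion lists what the trial is meant to show, as five two-arm statements: B equivalent to A; "the efficiency of Bushen Huatan Decoction combined with metformin is superior to that of a single-use of metformin"; E (BSHTD plus Baduanjin) superior to B and to C; and E equal to D. The Statistical analysis section compares groups by ANOVA with Bonferroni correction and does not say over how many comparisons.

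**The concern.** The section reasons from one pairwise contrast and quotes the power of a different test. An omnibus F test asks whether any of five means differ; a significant result does not say which arm is better. The claims in the Discussion need pairwise tests, and the plan corrects those for multiplicity. If 90% is read as the chance of detecting the add-on effect, a null result for D against A, or for E against B, will be given more weight as negative evidence than it can bear. The β wording adds to the confusion, because a reader cannot tell whether 80% or 90% was the target.

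**Working it through.** **Inputs, all from Sample size calculation unless noted.** n = 30 completers per arm, two-sided α = 0.05, changes 0.40 (SD 0.24) and 0.57 (SD 0.27). Pooled SD = √[(0.24² + 0.27²)/2] = √0.06525 = 0.255.

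**1. The plan's own figure.** For the F test with 4 and 145 df, λ = n·Σ(μᵢ − μ̄)²/SD², with critical value 2.434.
- A = B = C = 0.40 and D = E = 0.57: Σ = 3(0.068²) + 2(0.102²) = 0.03468, λ = 15.94, power 90.1% (88.9% with 29 per arm). The Discussion supplies B = A and E = D; C = 0.40 is an assumption.
- One arm differing by 0.21: Σ = 0.8 × 0.21² = 0.03528, λ = 16.22, power 90.6%.
- One arm differing by 0.17: Σ = 0.02312, λ = 10.63, power 73%.
- A and D 0.17 apart, the rest midway: Σ = 2(0.085²) = 0.01445, λ = 6.64, power 50%.

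So 30 per arm reproduces for the F test under more than one pattern and fails under others. Attrition is handled correctly: 30/0.8 = 37.5, hence 38, and 5 × 38 = 190.

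**2. The contrast argued for, D against A.** Three candidate differences:
- Pilot: 0.57 − 0.40 = 0.17. In percentage terms this is 0.57/2.09 = 27.3% against 0.40/2.11 = 19.0%, or 8.3 points.
- Anticipated 30% against 20% on the pilot baselines: 0.30 × 2.09 − 0.20 × 2.11 = 0.205, or 10% of 2.10 = 0.21.
- 10% of the entry threshold of 2.29 (Inclusion criteria): 0.229, with the SD left unchanged.

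The standard error is 0.2554 × √(2/30) = 0.0660, so the noncentrality values are 2.58, 3.11 to 3.18, and 3.47. Power by noncentral t (58 df, and the ANOVA error df of 145):

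| Correction | 0.17 | 0.205–0.21 | 0.229 |
|---|---|---|---|
| None (0.05) | 72–73% | 86–88% | 93% |
| 3 superiority contrasts (0.05/3) | 55–56% | 74–78% | 84–85% |
| 5 Discussion comparisons (0.01) | 47–49% | 67–72% | 79–80% |
| All 10 pairs (0.005) | 38–40% | 58–63% | 71–73% |

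**3. Sensitivity at 0.17.** SD from 0.24 to 0.27 moves the unadjusted power from 77% to 67%. If all 38 per arm were evaluable, it would be about 82% unadjusted and 51 to 53% over ten pairs. Reaching 90% would take 49 completers per arm unadjusted, or 78 at α = 0.005.

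**4. Gain from baseline adjustment.** The pilot baseline and end SDs are 0.30 and 0.26. The implied correlation is r = (0.30² + 0.26² − SD_change²)/(2 × 0.30 × 0.26). This gives (0.1576 − 0.0576)/0.156 = 0.64 for A and (0.1576 − 0.0729)/0.156 = 0.54 for D. The residual SD, 0.26√(1 − r²), is 0.200 and 0.218, pooled about 0.21. D against A at 0.17 then has about 87% power unadjusted and about 59% over ten pairs.

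**The case against.** A good deal can be said for the plan, and much of it stands.
- The planned effect is the anticipated 10%, not the pilot 0.17. At 0.205 to 0.21 the unadjusted power is 86 to 88%, close to 90%. At 0.229 with the SD unchanged it is 93%, although if the SD rises in proportion to the baseline (0.2554 × 2.29/2.10 = 0.279) it is about 88%. A reader might take 72% and 40% as the power of the comparison; they are the lower part of a range.
- The Bonferroni family is not stated. Ten pairs is the heaviest reading, and three superiority contrasts is a fair alternative.
- β at an upper limit of 20% can be read as β of at most 20%, which 90% power satisfies. A reader might infer a flat impossibility; the text supports only an ambiguity.
- The F test is the first step of the planned ANOVA, so its power is not irrelevant. A condensed article may also leave the five means to the full protocol.
- A reader might infer that E against B, from the trial's title comparison, has no planning assumption. The Discussion's B = A and E = D imply 0.17 for it; only group C lacks a value.

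What these points do not remove is the gap between the test that carries the 90% and the corrected pairwise tests that carry the claims. Under every correction considered, and at all three differences, D against A with 30 completers per arm stays below 90%.

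**Conclusion.** The point holds as a mislabelled power statement, not as a miscalculated sample size. The 30, 38 and 190 are consistent with an F test, and it would be wrong to infer that they are errors or that only one pattern of means yields 90%. The 90% does not carry over to the pairwise hypotheses. For D against A the power is about 72% (pilot difference) to 86–88% (anticipated 10% on the pilot baselines) without correction. With Bonferroni it is 38 to 78% across those two differences, depending on whether three, five or ten comparisons are counted.

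These figures assume 30 completers per arm and the pilot SD of 0.255. The pilot baseline of about 2.1 lies below the entry threshold of 2.29, so both the effect and the SD may differ in the trial population. This should be fixed, but it does not by itself call for a larger trial.

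**What to change.** Four changes, none of which alters N:
1. Print a single β/power pair.
2. State that the 90% is omnibus power, and give the five assumed means and the SD behind it.
3. State the power for the pairwise comparisons as the range above, with the number of comparisons that the Bonferroni correction covers.
4. Analyse HOMA-IR with adjustment for its baseline value (ANCOVA). The baseline is already measured. The gain may be smaller than calculated, because admitting only women at or above 2.29 may lower the correlation between baseline and end values.

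Naming one primary contrast would avoid most of the multiplicity loss. That is an option for the sponsor, not a required correction. The cost is revised wording, a change of analysis model and a less favourable stated power.
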